### Participant timeline

The participant schedule through the study, including eligibility, consent, randomisation, baseline and follow-up assessment are highlighted in Fig. 1.

**Fig. 1 Fig1:**
[figure not shown]
Flow diagram of a participant journey through the SPACES feasibility trial

### Sample size

The sample size for a feasibility study should be adequate to estimate the uncertain critical parameters (SD for continuous outcomes; consent/recruitment rates, attrition, intraclass correlation coefficient (ICC)) needed to inform the design of the full RCT with sufficient precision. As a feasibility study we propose to recruit for a fixed time (T) and not a sample size (N). We propose to recruit for 6 months at between 4 and 7 sites (e.g.: 4 × 6 = 24 site*months of recruitment). We believe that in order for the main trial to be feasible we need to recruit enough participants to run a full SPACES intervention group in the intervention arm at each site (recruiting at least 2*6 = 12 participants) which would be a rate of 12/6 = 2 participants per site per month. There are several flat rules of thumb for sample sizes for two-armed external pilot/feasibility trials ranging from 24 in total [31], to 30 [30, 32], to 50 or 60 [33], and 100 [34] and recruiting for 24 site*months should enable us to exceed these ranges (of 48 to 140 participants).

Interviews will be conducted with 15 participants from the intervention group and 5 intervention delivery staff members (see supplementary material for the topic guide). This sample size will be continuously evaluated during data collection process’ to ensure adequate qualitative sample size information power is met [35]. A combination of purposive and convenience sampling will be utilised to ensure adequate and varied sampling across all involved NHS sites (2–4 participants and × 1 PAC per site) from the cohort of participants and delivery staff available.

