### Recruitment

#### Recruitment of NHS sites

Sites were recruited to the SPACES programme via email invitation. Emails were sent to all mental health NHS Trust teams who had provided a letter of support for the SPACES grant application, with details of the SPACES feasibility trial. In addition, mental health NHS Trust teams with a working relationship to the research team were also approached as potential sites. Seven trusts responded to the call, at which point further information was provided regarding the trial and clarification was offered to any questions trusts had about the trial. One site was lost during this process, leaving six trusts to participate in the SPACES feasibility trial.

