#### Methods for additional analyses (e.g., subgroup analyses)

Qualitative data will be analysed utilising an inductive approach and thematic analysis [40] to explore both participants and intervention delivery team experiences of the SPACES intervention. Participant data will be categorised to understand different perspectives. Qualitative analysis software, NVivo, will be used to process and analyse the data. Feedback from both participants and PACs will inform refinement of the intervention, including the intervention manual and training, with the aim to improve the acceptability and feasibility of the SPACES intervention.

Critical variables to enable success in the full RCT (workstream 3) will follow a traffic light system with recruitment of 100%, i.e., an average of 2 participants per centre per month being green, 50–99% (1 – 1.9 participants per month) being amber, and below 50% being red. This will enable us to select the correct number of centres for the full RCT. We will also test our ability to achieve follow-up at our target rate in the feasibility study, and to ensure there is equal retention between arms.

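### At the only recruitment rate stated, 24 site-months give 48 participants, which does not exceed the cited rules of 50, 60 and 100, and the basis for the upper figure of 140 is not given

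*Protocol article*

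**What the plan says.** The Sample size section of the protocol article sets recruitment by duration: "we propose to recruit for a fixed time (T) and not a sample size (N". The duration and sites follow: "We propose to recruit for 6 months at between 4 and 7 sites (e.g.: 4 × 6 = 24 site*months of recruitment". The requirement per site is one full intervention group plus an equal number of controls, "recruiting at least 2*6 = 12 participants", "which would be a rate of 12/6 = 2 participants per site per month". The traffic-light criteria, under Methods for additional analyses, use the same rate again: "an average of 2 participants per centre per month being green".

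The section then cites rules of thumb for two-arm pilot trials, "ranging from 24 in total [31], to 30 [30, 32], to 50 or 60 [33], and 100 [34", and concludes that "recruiting for 24 site*months should enable us to exceed these ranges (of 48 to 140 participants". Under Recruitment of NHS sites, one of seven responding trusts was lost, "leaving six trusts to participate in the SPACES feasibility trial".

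**The concern.** The closing sentence ties a definite amount of recruitment (24 site-months) to a definite result (exceeding every listed rule, with 48 to 140 participants). The lower figure is itself below three of the rules it is said to exceed, and the upper figure has no derivation.

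The section opens by requiring a size that estimates the SD, the recruitment and attrition rates and the ICC with sufficient precision, and the rules of thumb are its only numerical benchmark for that. A reader judging how well the trial can inform the main-trial sample size would take from this sentence that even the four-site design passes 100. On the stated rate it does not.

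**Working it through.** **Inputs.** From Sample size: 6 months of recruitment, 4 to 7 sites, at least 12 participants per site (2 per site per month), and rules of 24, 30, 50, 60 and 100. From Intervention description: groups of 6 to 12. From Sequence generation: 1:1 allocation. From Recruitment of NHS sites: six trusts.

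**Formula.** N = sites × months × rate per site per month.

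**The plan's own figures.** The lower one reproduces exactly: 4 × 6 × 2 = 48. The upper one does not: the largest permitted design at the stated rate gives 7 × 6 × 2 = 84.

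**All permitted numbers of sites.** The last column assumes one group of 12 per site, so 24 recruits per site over both arms (4 per site per month).

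| Sites | Site-months | N at 2 per site per month | Rules exceeded at that rate | N with full groups of 12 |
|---|---|---|---|---|
| 4 | 24 | 48 | 24, 30 | 96 |
| 5 | 30 | 60 | 24, 30, 50 (equals 60) | 120 |
| 6 | 36 | 72 | 24, 30, 50, 60 | 144 |
| 7 | 42 | 84 | 24, 30, 50, 60 | 168 |

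**Rates needed over 24 site-months.** To reach 50: 50/24 = 2.08 per site per month. To reach 60: 60/24 = 2.50. To reach 100: 100/24 = 4.17. To reach 140: 140/24 = 5.83.

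**Where 140 could come from.** At four sites it means 140/4 = 35 per site, or 17.5 in the intervention arm, which is more than one group of at most 12 can hold. At seven sites it means 140/42 = 3.33 per site per month, or 20 per site. That is a group of 10 plus 10 controls: 7 × 20 = 140. Six sites with groups of 12 give 144. Both use more than 24 site-months and more than 2 per site per month.

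**Two readings of the parenthesis.** If 48 to 140 is meant as the span of the cited rules, it disagrees with the listed 24 to 100. If it is meant as expected recruitment, which the match at 48 suggests, its lower end does not exceed 50, 60 or 100. The sentence needs correcting on either reading.

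**Illustration of precision.** The article gives no follow-up rate. If 80% is assumed, the 95% half-width is 1.96 × √(0.8 × 0.2/N): 11 points at N = 48, 9 at N = 72 and 7 at N = 140. If 80% also have valid 6-month accelerometer data (n = 38 and 57, chi-square with n − 2 degrees of freedom), the 95% limits for an SD are about −19% to +30% at N = 48 and −16% to +23% at N = 72. The arithmetic finding does not rest on these figures.

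**The case against.** The strongest reply is that 2 per site per month is a floor. The section asks for at least 12 per site, and groups may hold up to 12 people, so recruitment could run well above 2. The range could then describe four sites at the minimum up to seven sites with larger groups. This has force. A reader might infer that 140 is impossible, and the documents do not support that, because seven sites with groups of 10 give exactly 140. A reader might also infer that expected size is overstated by 67% (140 against 84). That compares an upper figure with a minimum, so it does not measure an overstatement. What the reply does not rescue is the sentence as written. It attaches the range to 24 site-months, where one full group of 12 at each of four sites still gives only 96, and it does not state the larger sites and rate.

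A second reply is that 24 site-months is only an example and that six trusts take part. That also stands: at the minimum rate six sites give 72, above every cited rule except 100.

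A third reply is that little depends on the total. Recruitment is by fixed time, the analysis is mainly descriptive with interval estimation, and the recruitment progression criterion is a rate. This is right, and it limits the seriousness of the point.

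**Conclusion.** The sentence is wrong as written. At the stated minimum rate 24 site-months yield 48, which exceeds two of the five cited figures (24 and 30). The permitted range of sites yields 48 to 84, and none reaches 100. The figure of 140 is attainable in principle, but only with more sites and a higher rate than the sentence uses. These conclusions assume 6 months of recruitment and, for the 96, one intervention group per site.

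It would go too far to conclude that the sample-size rationale collapses or that the trial is too small. The rationale also rests on fixed-time recruitment and on filling one group per site, and the article sets no precision target that 48 or 72 could be shown to miss. Severity is minor to moderate: the stated size becomes less favourable, while no analysis or progression rule changes.

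**What to change.** Replace the closing sentence on the rules of thumb with wording such as:

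> If the minimum target of 2 per site per month is met for 6 months, we expect at least 48 participants with four sites and 84 with seven, and 72 with the six participating trusts. This exceeds 24 and 30 at four sites, reaches 60 at five, exceeds 60 at six or seven, and does not reach 100.

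Then either state the number of sites and the rate behind 140, for example seven sites with groups of 10 if that was the intention, or delete the figure. Deleting it without checking could remove a legitimate upper bound.

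The cost is wording only, and no extra participants are needed. Trial status reports recruitment and follow-up as complete, so the correction serves the published record and readers who use the trial's SD, rates and ICC to size the main trial.

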### Recruitment

#### Recruitment of NHS sites

Sites were recruited to the SPACES programme via email invitation. Emails were sent to all mental health NHS Trust teams who had provided a letter of support for the SPACES grant application, with details of the SPACES feasibility trial. In addition, mental health NHS Trust teams with a working relationship to the research team were also approached as potential sites. Seven trusts responded to the call, at which point further information was provided regarding the trial and clarification was offered to any questions trusts had about the trial. One site was lost during this process, leaving six trusts to participate in the SPACES feasibility trial.

### Recruitment of participants

Participants will be identified via secondary care through Community mental health teams (CMHT) or via primary care practices. General Practitioner (GP) surgeries and CMHTs will be asked to consult their patient lists to screen against the inclusion and exclusion criteria (see eligibility criteria section) for potentially eligible participants. Participants with a documented diagnosis of SMI are eligible to participate regardless of whether they are under the care of a mental health NHS trust or not. Participants identified as potentially suitable for the SPACES trial will be provided with a copy of the patient information pack via the post or by their GP/ CMHT directly. The patient information pack will contain an invitation letter, participant information sheet, a consent to contact (CTC) form, and a pre-paid return envelope. If interested, the potential participant will either return the CTC form to the SPACES research team in the pre-paid envelope or the recruiting clinician will complete a verbal CTC form on behalf of the potential participant and return it to the SPACES study team by email, post or pass the details to a SPACES researcher over the phone. In addition, members of CMHTs and GPs or practice nurses will be invited to directly refer eligible patients to the SPACES team during any encounter they have with the potential participant (e.g., face to face or telephone appointments). CMHT/ GP surgeries members will be provided with patient information packs to give to service users who are receptive to participating in the SPACES trial. The pack will either be provided directly at a face-to-face meeting, electronically, or via the post if the meeting was over the phone. CMHT members, GPs or practice nurses can gain verbal CTC from potential participants during these encounters and pass on their information to the SPACES team if verbal CTC is provided.

Posters and flyers advertising the study will also be placed in centres which are recruiting to the study. In addition, posters may also be displayed on participating trust’s Facebook pages and Twitter accounts. Patients interested in taking part in the study will be asked to approach their care coordinator for further information about the study, and if eligible and appropriate will be given a patient information pack.

On receipt of a completed CTC, a SPACES researcher will contact the potential participant to discuss the study and provide an opportunity to answer any questions and, if appropriate, arrange for consent to be taken if they are happy to participate given the study information provided.

To ensure the suitability of people prior to recruitment, the GPs or CMHTs of each potential participant will check they meet the eligibility criteria. This will be done prior to the potential participant being approached by the SPACES research team.

### Assignment of interventions: allocation

#### Sequence generation

Allocation will be through block, 1:1 randomisation (with random permuted blocks of various integer multiple of two sizes) with a separate schedule for each site. There will be no additional stratification factors, beside site, in the randomisation sequence. The study statistician in Sheffield CTRU will generate the randomisation schedule prior to the start of the study using its own web-based in-house CTRU (SCRAM) randomisation system.

#### Concealment mechanism

Allocation concealment will be ensured; the web-based system is secure and will not release the randomisation code until the patient has been recruited into the trial, which takes place after all baseline measurements have been completed. The sequence generation is conducted by the study statistician who is not involved in randomising and details of block sizes will not be communicated to the study team.

#### Implementation

The study statistician will generate an allocation sequence. At the second baseline data collection point (accelerometer return), the SPACES researcher will contact the SPACES central team to be provided with the participant’s randomisation assignment. Participants are then told their allocation.

### Assignment of interventions: blinding

#### Who will be blinded

By the nature of the interventions used within this study, blinding of the participants, clinicians and the researchers is not possible. However, those involved in the analysis of the data will be blind to group allocation whilst the trial is ongoing and until the analysis is complete.

#### Procedure for unblinding if needed

Study personnel who are responsible for analysing data and reporting results will remain blinded throughout the study period. As clinicians and researchers are not blinded to allocation there will not be a need for unblinding.

### Data collection and management

#### Plans for assessment and collection of outcomes

Data collection will take place across three time points; baseline, and three- and six-months post-randomisation. Participant 1:1 randomisation occurs immediately after baseline data collection is complete. At baseline only, demographic and medical history information will be collected. At baseline, and the 3- and 6-month follow-ups, primary and secondary outcome data will be collected by a SPACES researcher at a face-to-face meeting in NHS premises, the participant’s home or another mutually convenient location. If for any reason a participant is not able to meet face-to-face, where possible data will be collected over the phone, by postal questionnaire or via an online questionnaire. See data collection schedule for more details (Table 1).

Physical activity and sedentary behaviour data will be gathered using Actigraph GT9X Link or Axivity AX6 accelerometers.^1^ Participants will be asked to wear the accelerometer for 10 days prior to each data collection point (baseline, three- and six-month follow-up). Accelerometers will be provided and collected from participants at each data collection point.

#### Plans to promote participant retention and complete follow-up

The following plans will be utilised in order to promote participant retention throughout the trial period:Regular communication with study participants will be provided throughout the study, with participants being provided with NHS site SPACES team contact details for any potential queries.If a questionnaire is returned incomplete or contains errors, a researcher will call the participant for clarification or completion of missing data.Participants will be advised that they are able to contact a member of the research team if they require assistance with completing a questionnaire.Participants will be asked to provide contact details of up to three people who can be contacted if the SPACES team are unable to contact the participant directly.

In order to understand the feasibility of the trial, study withdrawal and dropout rates will be monitored and recorded. Participants will be informed that they may withdraw from the study at any time without influencing their future care or treatment. When a participant wishes to withdraw from the study, we will confirm the withdrawal type from one of the following possible options:Where a participant in the intervention arm of the study wishes to withdraw from the study intervention, but is prepared to continue completing follow-up questionnaires (i.e., no further intervention sessions are attended but follow up data is still collected). This is classed as ‘Withdrawal from the intervention’.Where a participant in the intervention arm of the study wishes to withdraw from completing any further follow-up data but wishes to continue with the intervention This is classed as ‘Withdrawal from follow-up’.Where a participant in the intervention arm wishes to withdraw from both the study intervention AND from completing any further follow-up data collection. This is classed as ‘Full withdrawal’. Where a participant in the usual care arm wishes to withdraw from follow up this is classed as full withdrawal.

### Data management

Data management will be provided by University of Sheffield Clinical Trials Research Unit (CTRU) who adhere to their own Standard Operating Procedures (SOPs) relating to all aspects of data management, including data protection and archiving. The study will use the CTRU's in-house data management system (Prospect) for the capture and storage of study-specific participant data. Access to Prospect is controlled by usernames and encrypted passwords. Designated staff at each site will enter data from source documents into the Prospect database. Once data have been entered, electronic validation rules are applied to the data on a regular basis; discrepancies are tracked and resolved through the database. All collection, storage, processing and disclosure of personal information will be performed in compliance with the GDPR & Data Protection Act 2018.

### Confidentiality

Participants will be informed of their right to confidentiality. All information collected during the study will be kept strictly confidential. Information will be held securely in paper and/or electronic formats at either the Sheffield CTRU, University of Sheffield, or Department of Health Sciences, University of York. All participants will be anonymised at the point of consent, by assignment of a study number. This will ensure that all personal data collected for the study are anonymous. Personal data and anonymised data will be stored separately in a restricted access folder on a secure university server, access will be password protected, and restricted to members of the SPACES research team. Quotations from participants may be used in research reports and other publications and presentations; however, care will be taken to protect the anonymity of participants so that others are not able to identify them.

### Statistical methods

#### Statistical methods for primary and secondary outcomes

As the trial is a pragmatic parallel group RCT design the statistical analysis will be performed on an intention-to-treat-basis and will be reported and presented according to the CONSORT statement extension to feasibility trials [36]. As a feasibility study the analysis will be mainly descriptive and focus on confidence interval estimation and not formal hypothesis testing.

We will use the data from this feasibility study, including reported rates of consent, recruitment and follow-up, and outcome measures, accelerometer-assessed minutes of MVPA per day (averaged over all available valid days), accelerometer-assessed total physical activity and minutes per day of sedentary behaviour (averaged over all available valid days), BMI, AIM, PHQ-9, SF-12, SIMPAQ, EQ-5D-5L, ReQoL to summarise overall and by randomised group, to inform sample size estimation for the main trial.

Accelerometer parameters will include daily 16-h per day wear time to constitute as valid wear time, intensity gradient cut off points of < 30 mg, 30–100 mg, 101–400 mg and > 400 mg (inactive, light, moderate and vigorous activity respectively). Mean MVPA per day is calculated on 5-s epochs with a 1-min bout duration, inclusion criteria of > 80%. All days (≥ 4 valid days), weekends (≥ 1 valid days) and weekdays (≥ 3 valid days) will be calculated. Mean acceleration and intensity gradients will also be reported. ActiGraph GT9X link [37] and Axivity AX6^1^ [38] accelerometers will utilise 100-Hz measurement frequency rates. Accelerometer data will be processed using GGIR v2.4–0 [39] in R [http:/cran.r-project.org].

We will also include, as part of the feasibility analysis, estimation of the effect size for accelerometer-determined physical activity 6-months post-randomisation (the probable primary endpoint for the definitive study), defined as the mean (averaged over all available valid days) minutes of MVPA per day, with confidence interval estimates to check that the likely effect is within a clinically relevant range (as confirmation that it is worth progressing with the full trial (i.e. 95% CI includes a difference of 6 min of MVPA per day)). For this we will use a partially clustered mixed effects model with 6-month minutes of MVPA as the outcome and baseline minutes of MVPA, site and randomised group as fixed effects and SPACES intervention groups as random effects. The ICC from this model will be reported and will inform the ICC estimate for the main trial. This information along with the acceptability of the study design and protocol to patients/GPs; the safety of the intervention; adherence to the intervention, patient recruitment and attrition/retention rates will enable us to determine whether or not the definitive RCT is feasible, within a satisfactory timescale and cost envelope using UK sites alone.

We will estimate the intervention costs based on the delivery of the related activities and the study records over the intervention period. We will also test the feasibility and acceptability of the bespoke health care and service use questionnaire. Analysis of the completeness of participants’ responses and use of listed services together with additional services recorded by participants, will enable further revision to collect most relevant data in the full RCT and eliminate questions with few responses. The completeness and descriptive statistics of healthcare resources and EQ-5D-5L will be summarised by participants’ allocated study arm. No formal cost-effectiveness analysis will be undertaken as the feasibility study is not sufficiently powered.

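### A 95% CI that includes 6 min/day of MVPA is called confirmation that the full trial is worth running, but it shows only that 6 min/day is not ruled out, and a CI wholly above 6 fails as worded

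*Protocol article*

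**What the plan says.** Under Statistical methods for primary and secondary outcomes, the Protocol article plans to estimate the intervention effect on accelerometer MVPA six months after randomisation, "defined as the mean (averaged over all available valid days) minutes of MVPA per day". The estimate comes from a "partially clustered mixed effects model with 6-month minutes of MVPA as the outcome", adjusted for baseline MVPA and site, with intervention groups as random effects.

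The estimate and its interval are used "to check that the likely effect is within a clinically relevant range". The sentence goes on to describe this check "as confirmation that it is worth progressing with the full trial" and defines it as "95% CI includes a difference of 6 min of MVPA per day". It sets no condition on the point estimate, the lower limit or the width of the interval, and makes no provision for an interval wholly above 6.

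The same section says the analysis will "focus on confidence interval estimation and not formal hypothesis testing". It also lists acceptability, safety, adherence, recruitment and retention as considered together with the MVPA result when judging whether the definitive trial is feasible. A separate traffic-light rule for recruitment appears under Methods for additional analyses.

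**The concern.** A confidence interval that contains a value is compatible with that value. It does not show that the value is likely, and a wide interval is compatible with many others, including zero and harm. Using inclusion of 6 as confirmation therefore reads absence of exclusion as support. It also rewards imprecision: fewer participants, more missing accelerometer data or a larger ICC all widen the interval and make the criterion easier to meet.

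The criterion is also two-sided in a way the purpose is not. An interval of 7 to 17 min/day does not include 6 and so fails as worded, although it is a better result than many that pass.

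What is at stake is how the feasibility result is reported and carried into the case for the full trial: a null or unfavourable estimate with a wide interval could be presented as having confirmed that a full trial is worth running.

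**Working it through.** **Inputs from the article.** The threshold is 6 min/day with a two-sided 95% CI (Statistical methods). Allocation is 1:1 ("Allocation will be through block, 1:1 randomisation", Sequence generation). The expected total is 48 to 140 (Sample size). The lower figure reproduces: 4 sites × 6 months × 2 per site per month = 48. Six trusts remained (Recruitment of NHS sites), which at the same rate gives 6 × 6 × 2 = 72. The article states no power, error rate or pass probability for the 6-min criterion, so there is no figure of its own to reproduce on that.

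**Assumed inputs.** The article gives no SD for MVPA; the study is meant to be "adequate to estimate the uncertain critical parameters (SD for continuous outcomes" among other things. The residual SD is taken as 15–30 min/day, with 10 as a lower sensitivity value. The follow-up target is not given, so 80% analysed is assumed. Clustering is ignored; any positive intervention-group ICC would widen the interval.

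**Without an SD.** The criterion is met when the estimate lies within 6 ± 1.96·SE. Estimates of zero or below are accepted once 1.96·SE exceeds 6, that is SE > 6/1.96 = 3.06 min/day. At SE = 3.06 a true null is accepted with probability Φ(3.92) − Φ(0) ≈ 0.50, and more often at any larger SE. At a true difference of exactly 6 it is accepted about 95% of the time, whatever the sample size.

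**With an SD.** Let n = 0.8N, SE = SD·√(4/n) and h = t(0.975, n−8)·SE. The 8 is the number of fixed effects with six sites. For a true difference d,

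P(pass | d) = Φ((6 + h − d)/SE) − Φ((6 − h − d)/SE).

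For N = 72 and SD 20:
- n = 57.6; SE = 20·√(4/57.6) = 5.27; h = 2.009 × 5.27 = 10.6. Estimates from −4.6 to +16.6 pass.
- d = 0: Φ(3.15) − Φ(−0.87) = 0.81.
- d = −6: Φ(4.29) − Φ(0.27) = 0.39.
- d = +12: the interval lies wholly above 6 with probability 1 − Φ(0.87) = 0.19.

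Probability of meeting the criterion, at true 0 / true −6:

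| N | SD 10 | SD 15 | SD 20 | SD 30 |
|---|---|---|---|---|
| 48 | 0.57 / 0.05 | 0.79 / 0.33 | 0.87 / 0.57 | 0.92 / 0.79 |
| 72 | 0.39 / <0.01 | 0.69 / 0.15 | 0.81 / 0.39 | 0.89 / 0.69 |
| 140 | 0.12 / <0.01 | 0.45 / 0.01 | 0.65 / 0.12 | 0.82 / 0.45 |

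**Under a one-directional version (upper limit at or above 6).** P = 1 − Φ((6 − h − d)/SE). For N = 72 and SD 20 this is 1 − Φ(−0.87) = 0.81 at d = 0 and 1 − Φ(0.27) = 0.39 at d = −6, the same as before. At d = +12 the 0.19 that failed for lying wholly above 6 now pass.

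**The case against.** The strongest reply is that this is not a gate. The MVPA result is weighed with acceptability, safety, adherence, recruitment and retention; the section on the primary outcome measure says feasibility is judged mainly on recruitment; and the only graded thresholds are the recruitment traffic lights. No sentence says the programme stops or proceeds on the interval alone. That stands, and it limits the consequence. It does not turn inclusion of 6 into confirmation, and none of the other inputs addresses the effect on MVPA.

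Second, the above-6 failure looks like a slip of wording, since such an interval plainly serves the stated purpose. That is probably right. A reader might infer that the plan would reject a highly effective intervention; the article does not support this, because nothing suggests the team would act on the literal wording in that way.

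Third, a reader might infer that most null and many harmful results pass. This cannot be said without conditions. The relevant SD is the residual SD after baseline adjustment, in a less active population with very active people excluded, and the article does not give it. At SD 10 most nulls fail at 72 and 140 recruited, and at SD 15 with 140 recruited a true −6 passes about 1% of the time.

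Finally, little power to stop is expected in a study sized to estimate design parameters, and accepting a true 6 about 95% of the time is a defensible aim. That also stands, and it is a reason for a modest claim.

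**Conclusion.** The concern holds in a limited form. As written, the criterion supports only the statement that 6 min/day has not been excluded; it is easier to meet with less precision; and its literal wording fails an interval wholly above 6. None of this depends on an assumed figure.

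The size does. With residual SD 15–30, 80% analysed, 48–140 recruited and no clustering, a true null passes 45–92% of the time and a true −6 about 1–79%. At SD 10 the null range is 12–57%. Because the check is one input among several and the remedy is a restatement of what may be concluded, the severity is moderate, not must-fix.

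**What to change.** Restate the check in one direction. If the upper 95% limit is below 6 min/day, a relevant effect is ruled out and this counts against progressing. If the upper limit is 6 or more, including when the whole interval lies above 6, a relevant effect is *not ruled out*. Use that phrase in place of the claim of confirmation, and report the estimate and interval width beside it.

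This is one sentence in the protocol or analysis plan, with no new data and no design change. Follow-up is complete according to Trial status, so in practice it governs how the result is interpreted and reported. The cost is a more modest claim. It corrects the conclusion drawn and the above-6 case but does not lower the pass rate under a null or harmful effect; doing that would need a further condition, for example on the point estimate, which is a separate choice for the team.
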